**Fig 3 pone.0324648.g003:**
[figure not shown]
Study schema. *Participants who decide to discontinue CBD after the 26-week interim review visit but remain on study will form the SoC treatment arm. These participants will taper off CBD and complete a safety follow-up. ^†^Participants who decide to discontinue CBD after the 52-week final review visit will taper off CBD and complete a safety follow-up. For participants who wish to remain on CBD after the study, the 52-week final review visit is the last study visit. CBD: cannabidiol; SoC: standard of care.

During the first 26 weeks of treatment, participants will receive open-label CBD treatment in addition to the SoC. This treatment period consists of the following two phases: a 4-week titration period, during which the CBD dose will be titrated up to the participant’s optimal maximum dose (study site staff will train the participants or caregivers on how to dose and titrate CBD), and a 22-week maintenance period, during which the participants will maintain their optimal dose of CBD. Following a review after the first 26 weeks of treatment, participants will have the option to either continue adjunctive CBD treatment for another 26 weeks or discontinue CBD while maintaining their SoC treatment. Participants who choose to discontinue CBD after a 26-week interim review visit will be gradually withdrawn over a 10-day taper period and complete an end-of-taper visit and a follow-up safety assessment.

Participants who choose to continue treatment with CBD will maintain their dose for the remainder of treatment period 2, until the 52-week final review visit, which will also be the last study visit. Participants who do not continue CBD (outside of the study) after the 52-week final visit will undergo a 10-day taper period and complete an end-of-taper visit and a follow-up safety assessment. Participants will have the option to complete all study visits either at the study site or virtually (e.g., via telehealth or videoconference).

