### Statistical analysis

EpiCom is an exploratory study, so no formal statistical hypothesis will be tested. Ranking is not assigned to the study endpoints; therefore, no hierarchical testing strategy or other multiplicity adjustments will be considered. Given that the study is not controlled, no direct causal attribution of any observed association to CBD treatment will be made based on study findings. The study is not designed to distinguish whether improvements in TAND outcomes are due to CBD treatment or if they are the result of seizure reduction. A modelling approach will be used to explore the extent to which the observed associations of CBD treatment with TAND endpoints is associated with the change in seizure frequency during follow-up. Its marginal/causal effects may be further investigated with an exploratory mediation analysis [64].

Outcomes will be reported using standard descriptive statistics for continuous variables, including 95% CIs for the mean (including SD) or median (including the first and third quartiles, and the minimum and maximum values) change. Counts and percentages will be reported along with the 95% CI of the rate. Statistics will be presented overall and by age, where applicable. If provided, *P* values will be declared as nominal. An intermediate analysis at week 26 will be performed to describe any early trends.

A generalized linear mixed model (GLMM) will be used to evaluate the significant change from baseline to week 26 in effectiveness endpoints, adjusted by the assessment at baseline and age at baseline. During the second treatment period, summary statistics for endpoints may be computed for and between the CBD treatment and SoC arms. At week 52, a GLMM will be used to describe the association of treatment with change from baseline in effectiveness endpoints, adjusted by assessment at baseline, and a propensity score calculated based on age at baseline, sex, percentage change from baseline at week 26 in seizure frequency, 28-day average seizure-free days at week 26, and the number of concomitant ASMs. Least-squares means of the treatment effect (CBD vs SoC), two-tailed 95% CI and the unadjusted *P* values will be generated if at least 25% of the participants reaching the 26-week interim review will opt for SoC treatment in the second treatment period.

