## Discussion

There is an increasing focus on incorporation of “patient experience data” into decision-making for clinical trials and drug development process [63]. Including patient experience information in trial design gives patients a voice and allows for evaluation of endpoints that are of importance to them and their families. The EpiCom study was designed to increase the potential for efficient study execution, data dissemination, and impact on patient care.

In addition to keeping patient and caregiver input at the center of the study design process, EpiCom aims to reduce the burden associated with trial participation by implementing a hybrid decentralized clinical trial (DCT) approach, in which participants will have the choice to attend the clinical trial site, conduct the assessments at home, or both. The DCT strategy allows for clinical trial activities to be conducted at locations other than traditional clinical trial sites, such as the patients’ homes or other locations remote from the clinical trial site (e.g., access to video call visits, home phlebotomy for blood collection, and home delivery of study drug), as well as the use of digital health technologies (e.g., access to assessment tools via their own mobile device or directly on the web). Using the DCT approach, more participants can access the investigational treatment, which in turn can support inclusion of a greater diversity of patient populations and increase efficiency by reducing the burden on caregivers and enhancing engagement among participants, thereby increasing patient recruitment and retention [65].

Highly purified CBD (Epidiolex^®^) is already an approved treatment for seizures associated with TSC in many countries; therefore, because of ethical considerations and based on advice from PAGs, EpiCom was designed as an open-label, single-arm trial to ensure that CBD is available to all eligible participants. The assessment tools were selected primarily on the basis of what the advisory panel members considered the most effective method for measuring outcomes that are of value to the participants of the trial. Other considerations were the validation status of the tools, their previous use in TSC or similar studies, and the time needed to complete the assessments and their complexity.

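### The week-52 contrast labelled CBD vs SoC compares continuing with stopping CBD after 26 weeks of CBD, and its baseline-referenced outcome carries period-1 behavioural differences into the comparison

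*Protocol article*

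**What the plan says.** All references are to the protocol article.

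- **Period 1 (Study design).** "During the first 26 weeks of treatment, participants will receive open-label CBD treatment in addition to the SoC". The Discussion confirms the design: "EpiCom was designed as an open-label, single-arm trial to ensure that CBD is available to all eligible participants".
- **Choice at week 26 (Study design).** "participants will have the option to either continue adjunctive CBD treatment for another 26 weeks or discontinue CBD while maintaining their SoC treatment". Those who stop "will be gradually withdrawn over a 10-day taper period".
- **Who the comparator is (note to Fig 3).** "Participants who decide to discontinue CBD after the 26-week interim review visit but remain on study will form the SoC treatment arm".
- **Week-52 model (Statistical analysis).** "a GLMM will be used to describe the association of treatment with change from baseline in effectiveness endpoints, adjusted by assessment at baseline". The model also adjusts for a propensity score built from age, sex, percentage change in seizure frequency at week 26, average seizure-free days at week 26, and number of concomitant ASMs.
- **Output (Statistical analysis).** "Least-squares means of the treatment effect (CBD vs SoC), two-tailed 95% CI and the unadjusted *P* values will be generated". This is produced only if at least 25% of participants reaching the 26-week review choose SoC.
- **Limit on inference (Statistical analysis).** Because the study is uncontrolled, "no direct causal attribution of any observed association to CBD treatment will be made based on study findings". Any P values are nominal.

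**The concern.** The label names a comparison of adding CBD to standard care with standard care alone. The two groups differ only in whether CBD was continued after week 26. An LS-mean difference with a confidence interval and P value under that label can mislead in both directions. A null could be taken to mean that CBD adds nothing to SoC, when both groups may have improved on CBD and the stoppers kept the gain. A positive result could reflect worsening after withdrawal but be presented as treatment benefit.

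The choice of reference visit raises a second issue. The groups separate at week 26, but change is counted from the pre-CBD baseline. Any behavioural difference between future continuers and future stoppers that built up in period 1 is then part of the contrast, although it cannot reflect a difference in treatment. The Abstract says the results will inform future studies, so a misnamed figure could be carried forward.

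**Working it through.** **1. The plan's own figures.** Sample size: 60 / (1 - 0.20) = 75, as stated. If 60 participants reach week 26, the 25% trigger is met at 0.25 x 60 = 15 SoC against 45 CBD. All 15 have been through the 26-week CBD period. The safety set requires at least one dose of CBD and the full analysis set builds on it, so nobody in the effectiveness analysis has gone without study CBD.

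**2. What the label would require.** Let D be the difference at week 52 between being on CBD throughout and never having received study CBD. Let r be the fraction of D that stoppers retain at week 52. Suppose, for this step only, that the groups are exchangeable at week 26. Then:

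contrast = D - rD = (1 - r) x D

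| r (assumed) | contrast as share of D |
|---|---|
| -0.2 (rebound) | 120% |
| 0 | 100% |
| 0.25 | 75% |
| 0.5 | 50% |
| 0.75 | 25% |
| 1 | 0% |

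The label is right only in the r = 0 row. The article gives no value for r and does not state that r = 0 is assumed. The table shows how the contrast depends on r; it does not estimate a bias.

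**3. What the reference visit adds.** Write Y0, Y26 and Y52 for an endpoint at baseline, week 26 and week 52. Then:

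Y52 - Y0 = (Y26 - Y0) + (Y52 - Y26)

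The between-group difference in change from baseline is therefore a period-1 part plus a period-2 part. Both groups are on CBD in period 1, so the first part cannot be an effect of CBD against SoC.

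- If the groups are exchangeable at week 26, the period-1 part has expectation zero, and measuring from baseline or from week 26 gives the same expected contrast.
- The groups are formed by participants' choice, so exchangeability is not assured. Suppose continuers had improved in period 1 by an amount d more than stoppers, and neither group changed afterwards. Without adjustment, the baseline-referenced contrast is d and the week-26-referenced contrast is 0.

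**4. Whether the stated adjustment removes the period-1 part.** Of the listed covariates, the week-26 ones that measure an outcome are both seizure measures. For ABC or TAND-SQ the only behavioural covariate is the baseline assessment, which precedes period 1. The period-1 behavioural part is removed only so far as the baseline score, seizure change, age, sex and number of ASMs happen to predict it. Its size cannot be derived from the article.

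**5. Whether the data for a week-26 reference exist.** Table 1 schedules ABC, TAND-SQ, CBCL/ABCL, ASR, PROMIS and the global severity scales at both weeks 26 and 52. For BRIEF, CSHQ, PSQI, PedsQL and PedsQL FIM it lists week 26 only, so the added comparison does not apply to them.

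**The case against.** The strongest defence is that the article is open about the comparator. The Fig 3 note defines the SoC arm as those who discontinue, and the Abstract and Study design describe the same choice. The sentence giving the output itself refers to SoC in the second treatment period. On this view, CBD vs SoC is shorthand for period-2 treatment. The study is exploratory, P values are nominal, the model is said to describe an association, and the contrast appears only if the 25% condition is met. The question of what follows starting CBD is addressed by the baseline-to-week-26 analysis.

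Most of this stands and lowers the weight of the point. It does not make the label right. The disclaimer rests on the lack of a control, which is a different matter from the comparator's earlier CBD exposure. Nowhere does the article say that the contrast is continuing versus stopping.

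Four stronger readings are tempting but not supported:

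- **That CBD versus SoC cannot be estimated at all.** It can under exchangeability and full washout without rebound; the fault is that the washout assumption is not stated.
- **That the bias is about half.** The SoC arm is on CBD, taper included, for 26 x 7 + 10 = 192 of 364 days (53%). That describes exposure. The contrast at week 52 depends on r, and this share does not appear in (1 - r) x D.
- **That the label contradicts the causal disclaimer.** Treatment effect is ordinary wording for a model term, and the model sentence speaks of association. The wording is loose, not contradictory.
- **That moving the reference visit cures the label.** It leaves (1 - r) x D unchanged. It addresses only the period-1 part in step 3.

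**Conclusion.** The point holds as a mislabelled contrast with a poorly matched reference visit, not as a concealed design fault. That the comparison is continued versus discontinued CBD follows from the article's own description and needs no assumption. How far it departs from CBD versus SoC rests on r, which is unknown: from 120% down to 25% of D for r from -0.2 to 0.75, given exchangeable groups. The second part, that period-1 behavioural differences enter the contrast, rests on the groups being self-selected and on the listed covariates containing no week-26 behavioural score; it cannot be sized from the article. Given the disclosure of the arm's make-up and the exploratory, nominal and conditional status of the analysis, this is a moderate-to-minor correction.

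**What to change.** - In the week-52 analysis and its tables, label the contrast as continued versus discontinued CBD after 26 weeks of CBD.
- State that neither a null nor a positive result will be reported as CBD versus SoC.
- Keep the Table 1 change-from-baseline summaries. For the between-arm comparison, also report change from week 26 to week 52 adjusted for the endpoint's week-26 value, for endpoints assessed at both visits.

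The cost is a wording change and one added analysis on data already scheduled for collection; sample size and visits are unaffected. The small downside is that the study will present no figure described as CBD versus SoC. The change does not remove bias from participants choosing their own arm, so the existing limit on causal attribution should stay.

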### Sample size

Planned enrollment is for 75 participants, such that 60 participants may be evaluable at the 26-week interim review (assuming a 20% withdrawal rate during the first treatment period). Participants will be considered evaluable for a given endpoint if they complete the endpoint assessment at baseline and at the 26-week interim review. Although not required, the study will attempt to enroll approximately 25 adult participants.

### Enrollment

Participants will be primarily recruited from TSC specialist clinics globally. The study will be conducted at approximately 20 sites across the US, the UK, Canada, and Poland (list of study sites available on https://clinicaltrials.gov). The study is estimated to run from June 2023 to January 2026, with intermediate analyses planned when patients have completed three or six months of study intervention.

### Ethical considerations

The study will be conducted in accordance with the consensus ethical principles derived from international guidelines including the Declaration of Helsinki and Council for International Organizations of Medical Sciences International Ethical Guidelines, International Council for Harmonisation Good Clinical Practice Guidelines, and the applicable laws and regulations of the participating countries. The protocol and amendments were approved by institutional review board or independent ethics committee and national regulatory authority (as applicable) before initiation. The protocol was approved by WCG Institutional Review Board in the United States; received favorable opinion from South Central – Oxford A Research Ethics Committee; and was approved by the Health Research Authority and Health and Care Research Wales in the UK. The protocol has also been approved by the European Union Clinical Trials Information System for Poland. Written informed consent will be obtained from all participants or the participants’ parent(s)/legally authorized representatives prior to any study-related procedures.

## Discussion

There is an increasing focus on incorporation of “patient experience data” into decision-making for clinical trials and drug development process [63]. Including patient experience information in trial design gives patients a voice and allows for evaluation of endpoints that are of importance to them and their families. The EpiCom study was designed to increase the potential for efficient study execution, data dissemination, and impact on patient care.

In addition to keeping patient and caregiver input at the center of the study design process, EpiCom aims to reduce the burden associated with trial participation by implementing a hybrid decentralized clinical trial (DCT) approach, in which participants will have the choice to attend the clinical trial site, conduct the assessments at home, or both. The DCT strategy allows for clinical trial activities to be conducted at locations other than traditional clinical trial sites, such as the patients’ homes or other locations remote from the clinical trial site (e.g., access to video call visits, home phlebotomy for blood collection, and home delivery of study drug), as well as the use of digital health technologies (e.g., access to assessment tools via their own mobile device or directly on the web). Using the DCT approach, more participants can access the investigational treatment, which in turn can support inclusion of a greater diversity of patient populations and increase efficiency by reducing the burden on caregivers and enhancing engagement among participants, thereby increasing patient recruitment and retention [65].

Highly purified CBD (Epidiolex^®^) is already an approved treatment for seizures associated with TSC in many countries; therefore, because of ethical considerations and based on advice from PAGs, EpiCom was designed as an open-label, single-arm trial to ensure that CBD is available to all eligible participants. The assessment tools were selected primarily on the basis of what the advisory panel members considered the most effective method for measuring outcomes that are of value to the participants of the trial. Other considerations were the validation status of the tools, their previous use in TSC or similar studies, and the time needed to complete the assessments and their complexity.

Importantly, both the TAND-SQ and the TSC-PROM are condition-specific measures and were developed in direct participation with a broad range of stakeholders from the TSC community. The TAND-SQ development, for example, included family members as active members of the TAND consortium throughout the process of development and validation of the tool [19,23]. Given that TSC is associated with a wide range of symptoms and affects multiple organs in the body, a “holistic” approach has been proposed to manage TSC and TAND-associated symptoms [6,66], with an emphasis on a systematic strategy to study and manage TAND symptoms, involving standardized approaches toward behavioral assessments and neuropsychological evaluations [4,6].

Collaborating with the TSC community enables focus on the clinical study objectives that are most important to the community, thus providing relevance to the study results, with the hope of affecting and adding value to patient care. The collaborative approach implemented for this study also increases the potential for efficient study execution and data dissemination. The option to withdraw from CBD treatment while still maintaining the SoC at 26 weeks may also improve patient/caregiver engagement, recruitment, and retention.

Beyond the questionnaires, we believe qualitative interviews may further improve and enrich the analysis of collected data. In the absence of group interviews, which had to be abandoned for logistical reasons, the caregivers are interviewed at 26 weeks using a short questionnaire that includes three free-text items to capture reasons for continuing or discontinuing CBD. This approach allows individual qualitative experiential findings to be linked to quantitative data. While the absence of group interviews represents a missed opportunity, qualitative group interviews should be incorporated as an integral part of future research in this area. Qualitative interviews during the study may further improve and enrich the collected data.

Given the multicountry nature of the study, descriptive data on patient characteristics by country may be evaluated as a post hoc analysis. In addition, the real-world nature of the study allows for any analysis on participant subgroup receiving concomitant medications to understand overall impact of these medication with CBD and TAND.

A limitation of the study is lack of a specific statistical strategy to measure the response bias and bias recalibration (change in response bias between two time periods). To mitigate this, the study’s statistical analysis uses a GLMM on repeated endpoints to quantify the magnitude of the dimension scale score’s difference from the baseline. The model accounts for within-subject correlation, confounding factors, and baseline assessments to reduce variability and the presence of reporting bias. Additionally, caregivers may have completely different views on the “severity-rating” of certain behaviors experienced. Such a subjective symptom under any circumstance would be challenging to standardize. To increase data accuracy, consistency and impartiality, several different questionnaires were included in the protocol to assess changes in the same nonseizure outcomes, including the patient’s most problematic behavioral symptom from clinician and caregiver perspectives. Also, to reduce intra- and interparticipant variability, training materials such as a behavioral severity discussion guide were designed in collaboration with PAGs to support discussions between study investigators and caregivers (who will be administering the assessments), to align on severity grading of the participant’s behavioral symptoms prior to formal consent and screening procedures.

We are continuing to work in partnership with an engaged and integrated patient/caregiver-HCP community that is enthusiastic and invested in the support of the clinical study delivery and interpretation. The use of the collaborative approach described here could serve as a blueprint to inform future studies evaluating potential pharmacotherapies for neuropsychiatric outcomes in TSC and similar populations. This study began enrolling participants from the US in June 2023. The UK, Canada, and Poland will soon follow. Last patient in is expected in the first quarter of 2025 with database lock in first quarter of 2026.
